### Statistical methods

Data will be entered into an SPSS (latest version) computer data-base using the registration number to identify the participant. All paper data will be stored in a secure locked cabinet, and all computer data will be stored on a secure server.

Baseline data will be analysed to describe the characteristics of the participants and to check for significant imbalance between the three groups. All outcomes will be analysed at each follow up assessment point (six, 24 and 36 weeks), and specific *a priori *hypotheses will be tested reflecting the outcomes that we expect to identify at the different stages. In each case a two sided test will be used. It is expected that t tests will be conducted to compare groups, unless any obvious deviations from t test assumptions are found in the outcomes, in which case the non - parametric Mann Whitney U test will be used.

In order to identify short term benefits, participants in the specialist rehabilitation groups (A and B) will be compared with participants receiving information pack only (group C) at six weeks. The null hypotheses will be tested, that there are no differences between the groups, with respect to change in patient disability, mobility and psychological wellbeing, and in carer strain. These hypotheses will be tested using each participant's change score from baseline (week 0) to week 6.

In order to identify medium term benefits, comparisons will be made at 24 weeks between pairs of treatment groups (Group A vs. Group B; Group A vs. Group C; Group B vs. Group C). The null hypotheses will be tested, that there are no differences between the groups with respect to change in patient disability, mobility, falls, speech, activities of daily living, social activities, psychological wellbeing, health related quality of life and use of health and social care services, and in carer strain, social activities and health related quality of life. These hypotheses will be tested using each participant's change score from baseline (week 0) to week 24.

In order to show loss or maintenance of benefit resulting from specialist rehabilitation, Group A (no ongoing support weeks 7 and 24) will be compared with Group B (ongoing support weeks 7 to 24) using the hypotheses in the medium term analysis and each participant's change score from week 6 to week 24.

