In order to identify longer term benefits, comparisons will be made at 36 weeks between pairs of treatment groups (Group A vs. Group B; Group A vs. Group C; Group B vs. Group C). The null hypotheses will be tested, that there are no differences between the groups with respect to change in patient disability, mobility, falls, speech, activities of daily living, social activities, psychological wellbeing, health related quality of life and use of health and social care services, and in carer strain, social activities and health related quality of life. These hypotheses will be tested using each participant's change score from baseline (week 0) to week 36.

An additional exploratory analysis will be performed using each participants change score for the above outcomes between week 24 and week 36. This is the follow-up period, and this analysis will provide evidence of trends in each group, and difference between groups, after all interventions cease in week 24.

It is recognised that multiple statistical tests are being undertaken, but no adjustments will be needed for multiple testing because *a priori *hypotheses have been stipulated, and the selective reporting of significant results will be avoided. Any additional exploratory (hypothesis generating) data analyses will make allowance for multiple testing in the usual way (Bonferroni).

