### Risks and adverse events

An adverse event (AE) is any unfavourable or unintended sign, symptom, syndrome or illness that develops or worsens during the period of the trial. A serious adverse event (SAE) is any adverse event which is life threatening, or results in hospitalisation, disability or death. AE and SAE will be identified by research or intervention team members, or reported by participants. They will be recorded, assessed for seriousness, expectedness and causality by clinical members of the research team and monitored. Any SAE deemed to be directly related to, or suspected to be related to the intervention and unexpected will be reported to the study Steering Group and the Ethics Committee.

Risks to participants from the trial are considered small, and no higher than those of usual care. The aspects of the MDT intervention delivered by the individual therapists are standard practice and aim to improve self awareness and management. Home visits will include assessment of home safety and aids and adaptations required which may require in improvements in safety for participants. However, it is possible that encouragement to exercise more could result in falls that might not otherwise have occurred. The MDT members experienced professionals and will emphasise safety issues to participants. The care assistants will be fully trained, and will work under the instruction of team professionals, in the support of patients and carers and the implementation of the agreed care plan. Other potential harms to the experimental groups include depression if raised expectations are not met, distress when additional input is stopped, and loss of support from family and friends if the additional care is perceived to reduce the need for informal support.

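### Falls, a harm the protocol itself names, are missing from the listed week-6 hypotheses, and where they are listed the fixed change score suits an event count poorly

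*Protocol article*

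**What the plan says.** - **Harm named.** Risks and adverse events states that "it is possible that encouragement to exercise more could result in falls that might not otherwise have occurred". The same section provides for adverse events to be recorded, assessed and monitored, and describes no comparison between groups.
- **Measurement.** Outcome measures, Table 1, lists falls as a patient outcome obtained by self report at baseline and weeks 6, 24 and 36. No recall window is given.
- **Week 6.** Statistical methods says that "participants in the specialist rehabilitation groups (A and B) will be compared with participants receiving information pack only (group C) at six weeks". At that point the listed hypotheses are "with respect to change in patient disability, mobility and psychological wellbeing, and in carer strain". Falls are not listed.
- **Weeks 24 and 36.** The lists at both points cover "change in patient disability, mobility, falls, speech, activities of daily living, social activities" and further outcomes, so falls are included, in three pairwise comparisons. The metric is fixed: "These hypotheses will be tested using each participant's change score from baseline (week 0) to week 24", and for the longer term "These hypotheses will be tested using each participant's change score from baseline (week 0) to week 36". The A versus B maintenance analysis applies the medium-term hypotheses to the change from week 6 to week 24.
- **Test.** A t test is expected, with Mann-Whitney as the fallback.
- **General rule.** The same section also says "All outcomes will be analysed at each follow up assessment point (six, 24 and 36 weeks").
- **Multiplicity.** Stipulated a priori hypotheses are not adjusted. "Any additional exploratory (hypothesis generating) data analyses will make allowance for multiple testing in the usual way (Bonferroni").

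**The concern.** The specialist team programme lasts six weeks, and week 6 is the first visit at which falls during it can be compared between groups. The listed week-6 hypotheses leave falls out although the item is collected then. The general all-outcomes sentence brings a falls analysis back in without saying whether it is one of the unadjusted a priori tests or an exploratory one subject to Bonferroni. For a possible harm this matters, because correction lowers the chance of detecting an excess and the choice could be made after the data are seen.

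The second difficulty is the metric. A disability score is a state at a visit, so follow-up minus baseline has a clear meaning. Falls are events over a period, so what a difference between two reports means depends on what period each report covers.

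The nurse-collected report deserves this care. It is taken on the same schedule in all arms, whereas adverse events are identified partly by intervention staff, who visit groups A and B at home but not group C.

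**Working it through.** The plan gives no fall rate, target difference or power for falls, so there is no figure of its own to reproduce. The check is a comparison of its statements, followed by arithmetic on stated assumptions.

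**1. Status of falls by analysis (Statistical methods)**

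| Analysis | Contrast | Falls listed? | Metric |
|---|---|---|---|
| Week 6 | A and B vs C | No; covered only by the all-outcomes sentence | Change 0-6 for listed outcomes |
| Week 24 | Three pairs | Yes | Change 0-24 |
| Maintenance | A vs B | Yes, through the medium-term list | Change 6-24 |
| Week 36 | Three pairs | Yes | Change 0-36 |
| Follow-up, labelled exploratory | Trends and group differences | Yes | Change 24-36 |

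**2. What the change scores cover.** The intervals between visits are 6 - 0 = 6, 24 - 6 = 18 and 36 - 24 = 12 weeks. The recall window has to be assumed:

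| Assumed recall | Left out of change 0-24 | Left out of change 0-36 |
|---|---|---|
| Since previous visit | Weeks 0-6: 6/24 = 25% | Weeks 0-24: 24/36 = 67% |
| Fixed three months (about 13 weeks) | Weeks 0-11: 11/24 = 46% | Weeks 0-23: 23/36 = 64% |
| Since baseline | Nothing | Nothing |

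The first row is plausible but unconfirmed. The only recall rule in the article, for service use under Economic evaluation, is the previous period, with three months before baseline.

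**3. Unequal windows.** With recall since the previous visit and a constant rate of λ falls per week, the 6-24 change is 18λ - 6λ = 12λ. A patient whose falling has not altered appears to worsen. This shift is expected equally in both groups if rates are equal, so it does not by itself bias the contrast, but the score cannot be read as a change in fall frequency.

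**4. Precision.** With equal windows and variances and baseline correlation r, the variance relative to the follow-up value alone is 2(1 - r) for a change score and 1 - r² with baseline as covariate:

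| r | Change score | Baseline as covariate |
|---|---|---|
| 0.2 | 1.6 | 0.96 |
| 0.3 | 1.4 | 0.91 |
| 0.5 | 1.0 | 0.75 |
| 0.7 | 0.6 | 0.51 |

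The covariate form is more precise at each value, and the change score is noisier than ignoring baseline when r is below 0.5. The documents do not give r.

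**5. What a week-6 comparison could detect (illustration).** Take 90 per group and 10% loss from Sample size calculations: 90 × 0.90 = 81 in C and 2 × 81 = 162 in A and B. Assume that 10% to 40% of group C fall at least once. Power of a two-sided 5% test of proportions:

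| Relative risk | Power, 10% to 40% fallers in C |
|---|---|
| 1.25 | 8% to 31% |
| 1.5 | 18% to 84% |
| 2.0 | 51% to nearly 100% |

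The comparison is feasible but could miss a modest excess, so an estimate with its interval says more than a significance test, and a Bonferroni correction would lower these figures further.

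**The case against.** The strongest reply is that a week-6 falls analysis is already planned: the all-outcomes sentence includes week 6, falls are measured then, and the contrast is set. That stands. A reader might infer that falls during rehabilitation get no planned comparison at all, and the text does not support this. Only a named hypothesis with a clear status is missing.

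A reader might also infer that Bonferroni would certainly be applied. The clause concerns additional exploratory analyses, and the only analysis expressly called that is the week 24-36 change. Whether an all-outcomes analysis outside the listed hypotheses counts as additional is not said. This is an ambiguity, not an established penalty.

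Third, the omitted shares rest on an unstated recall window and vanish if recall runs from baseline. Even with recall since the previous visit, the analyses taken together reach every period: week 6 covers 0-6, week 24 covers 6-24 and week 36 covers 24-36. That is fair. But no single listed comparison then counts falls since baseline, and the period of the team programme depends on the one analysis whose status is unclear.

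Fourth, the risk need not be confined to six weeks. Groups A and B keep the exercise fact sheets, and group B's care assistants follow the care plan for four more months. So part of the risk period does have named hypotheses.

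Finally, adverse event tabulation, recall wording and covariates may sit in a fuller protocol or analysis plan that is not shown. Their absence here is not criticised. The listed week-6 outcomes and the change-score metric, however, are fixed in this article.

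**Conclusion.** The point holds as a weakness in what the article fixes, not as a missing analysis. It rests on the text alone that a named possible harm is left out of the week-6 hypotheses, that the standing of the week-6 falls analysis is ambiguous, and that a change score is prescribed for an event count over intervals of 6, 18 and 12 weeks.

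The share of follow-up left out is conditional: 25% for 0-24 and 67% for 0-36 if recall runs since the previous visit, and none if it runs from baseline. A reader might infer that the change score biases the falls comparison. It does not, because the between-group contrast remains valid under randomisation. The loss is in interpretation, possibly in precision, and in a direct answer on falls since baseline. The primary outcomes are unaffected.

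**What to change.** 1. Name falls at week 6, A and B versus C, as a safety comparison, reported as an estimate with 95% CI and exempt from Bonferroni.
2. State the recall window used on the form.
3. In place of the change score, compare falls since baseline over weeks 0-6, 0-24 and 0-36 as a rate ratio with 95% CI from a count model (for example negative binomial) with baseline falls as covariate. Sum the visit reports where the recall windows allow it. Otherwise model the count in each recall window with the log of its length as offset.

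**Cost.** One further pre-specified comparison and some rewording, since the item is already collected at each visit. The trial is ongoing: if the form uses a different recall window, cumulative counts may not be recoverable for patients already assessed, and the offset version would have to serve for them.

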### Management and governance

The research team comprises a chief investigator (HG) with overall responsibility for the conduct of the research, two clinical principal investigators (BC, PT), a full time research manager (ST), a qualitative researcher (KB), a statistician (PW), research advisor (DW), and a co-ordinator of public and patient involvement (JK). All aspects of data collection and management are under the supervision of the research manager. The research team is supported in the delivery of the trial by an External Steering Committee, which meets twice per year to review progress and ensure timely completion of milestones. Membership of the EAG includes clinical experts, experienced researchers, a statistician, representatives from Parkinson's UK and the European Parkinson's Disease Association, local service providers and commissioners, and people with Parkinson's and carers. A separate PPI (Patient and Public Involvement) group, co-ordinated by a Parkinson's Specialist Nurse, helps the research team with the development of study documents and processes, and was involved in the planning stage of the project.

### Ethical and organisational review

Ethical approval has been granted to the Surrey Research Ethics Committee (application number 10/H1109/1). National Health Service Research and Development approval has been granted by four Participant Identification Centres.

## Discussion

The SPIRiTT trial is a community based MDT rehabilitation intervention for people with Parkinson's disease and their live-in carers. The intervention is delivered to people in their own homes, so that the costs and effectiveness can be compared with a similar intervention delivered to the same patient group in a day hospital setting. Findings will be compared with another community-based RCT, conducted in England recently that found no significant difference in outcomes or costs of patients receiving rehabilitation in a day hospital rather than in their own homes [66].

We anticipate several problems in the conduct of the trial and will put processes in place to avert or minimise their effect. First, retention of participants, particularly in the control group, may be difficult so we will seek to retain their interest by providing regular newsletters reporting trial progress. Patients randomised to the control group will be offered an MDT assessment and advice on completion of the trial follow up. Second, disruptions to the delivery of the MDT intervention may arise due to bad weather preventing travel, or staff sickness. We expect such interruptions will be minimal and consistent with a pragmatic approach to research on service delivery, and that cover will be available within the team for short term holiday or sickness leave. Third, lack of local NHS resources, due to financial exigencies, could impede the delivery of the intervention according to protocol to the numbers of patients and carers required by the sample size calculations, but we will liaise with local commissioners and providers to try and ensure their support. Fourth, recruiting MDT members and care assistants may be problematical, due to difficulties arranging temporary secondments from local providers, and local labour market conditions. We will address any staffing issues by advertising widely and offering favourable contracts for suitably qualified applicants. Lastly we may encounter difficulties in persuading live-in carers to take part in the research assessments, and we will seek to overcome this by explaining why their participation is important to the findings.

The trial investigates important issues in recent national policy recommendations for people with long term conditions, and Parkinson's disease in particular, and will provide guidance to inform local service planning and commissioning. The population of the study area is diverse and findings are more widely generalisable.

### Trial status

Ongoing

## List of abbreviations

AE: Adverse event; SAE: Serious adverse event; DeNDRoN: Dementia's and Neurodegenerative Diseases Research Network; DGH: District General Hospital; GP: General Practitioner; MDT: Multi disciplinary team; NHS: National Health Service; NICE: National Institute of Health and Clinical Excellence; PCRN: Primary Care Research Network; PNS: Parkinson's Nurse Specialist; QALY: Quality adjusted life years; SPIRiTT: Specialist Parkinson's Integrated Rehabilitation Team Trial
